### Interim analyses {21b}

No interim analysis is planned.

### Methods for additional analyses (e.g., subgroup analyses) {20b}

Not applicable

### Methods in analysis to handle protocol non-adherence and any statistical methods to handle missing data {20c}

Very few missing data are expected in the trial; however, in this case, any missing value of the primary endpoint will be replaced by the value reflecting failure. A sensitivity analysis to missing data will be performed using the maximum bias strategy.

In order to estimate some delays between two partially missing dates, if the day is missing, the day used will be the 15th (middle of the month). If both day and month are missing, value 1 for the day and value 7 for the month (middle of the year) will be used.

### Plans to give access to the full protocol, participant-level data, and statistical code {31c}

Such information may be made available upon specific request to the sponsor.

## Oversight and monitoring

### Composition of the coordinating center and trial steering committee {5d}

The trial steering committee, or “scientific board,” is composed of the principal investigators of the study, a methodologist, biostatisticians, a safety and pharmacovigilance manager, and a representative of the sponsor. This committee meets as required by the study. Its mission is to make any important decision at the request of the coordinating investigator concerning the proper conduct of the research and compliance with the protocol. It verifies compliance with ethics and keeps the Research Department informed of the progress of the research, any problems, and the results available. It decides on any relevant modification of the protocol necessary for the continuation of the research, in particular, measures to facilitate recruitment into the research, modifications of the research documents (protocol, informational and consent forms), decisions to open or close sites participating in the research, measures to ensure the best safety for the persons participating in the research, and discussion of the results and the strategy for the publication of the results. The scientific board may propose to extend or interrupt the research if the rate of inclusion is too slow, if too many patients are lost to follow-up, if there are major violations of the protocol, or for medical and/or administrative reasons. It specifies the possible modalities of prolonged follow-up of the participants included in the research. At the end of each meeting, the president of the scientific board must inform the sponsor of the decisions made. Decisions concerning a major modification or a budget modification must be approved by the sponsor.

### Composition of the data monitoring committee, its role, and reporting structure {21a}

An independent monitoring committee will not be necessary in this study because the treatment received by patients in the “experimental” group (i.e., alkalinized adrenalized lidocaine) will also, in our institution, be received by patients not enrolled in the study since this is also a part of our practice. Patients in the “control” group will only be exposed to treatment that is currently considered to be the gold standard.

### Adverse event reporting and harms {22}

The investigator is responsible for collecting all data related to adverse events that occur between the date of signing the consent form and the end of the participant’s participation. As part of this protocol, all adverse events must be collected. The investigator will report adverse events (clinical and biological) in the observation booklet. These adverse events will be sought at each visit during the study during the interview and clinical examination of the participant. The investigator must notify the Safety and Vigilance Unit by fax or email without delay from the day he/she becomes aware of any adverse event or any new fact related to any adverse event.

### Frequency and plans for auditing trial conduct {23}

An audit may be carried out at any time by persons mandated by the sponsor and independent of those conducting the research. The objective is to verify the safety of the participants and the respect of their rights, the respect of the applicable regulations, and the reliability of the data. An inspection may also be carried out by any competent authority (i.e., ANSM in France).

The audit, as well as the inspection, may apply to all stages of the research, from the development of the protocol to the publication of the results and the classification of the data used or produced in the framework of the research. Investigators agree to comply with the requirements of the sponsor for an audit and the competent authority for an inspection of the research.

### Plans for communicating important protocol amendments to relevant parties (e.g., trial participants, ethical committees) {25}

Any substantial modification, i.e., any modification likely to have a significant impact on the protection of persons, on the conditions of validity, and the results of the research, on the quality and safety of the products tested, on the interpretation of the scientific documents that support the conduct of the research, or on the methods of conducting the research, is the subject of a written amendment that must be submitted to the sponsor; the sponsor must obtain authorization from all regulatory agencies concerned prior to its implementation.

### Dissemination plans {31a}

The analysis of the data provided by the investigating centers is carried out by the USMR of the Bordeaux University Hospital. This analysis will lead to a written report that will be submitted to the sponsor, who will forward it to competent authorities.

Any written or oral communication of the results of the research must receive prior approval from the principal investigator and, if applicable, from any committee set up for the research. The principal investigator undertakes to make available to the public the results of the research, both negative and inconclusive and positive.

The publication of the main results will mention the name of the sponsor; of all the investigators who enrolled or followed participants in the research; of the methodologists, biostatisticians, and data managers who participated in the research; and of the members of the committee(s) set up for the research and the possible participation of the laboratory. The international rules of writing and publication (The Uniform Requirements for Manuscripts of the ICMJE, April 2010) will be taken into account.

In accordance with the law n°2002-303 of March 4, 2002, all participants will be informed, at their request, of the overall results of the research.

## Discussion

Anticipating a significant difference in favor of the lidocaine-bicarbonate group (group LEB), we deemed it ethical to include more patients in that group. As a result, randomization will be unbalanced with a 2:1 ratio, meaning that twice as many patients will be randomized to the experimental group.

Randomization is performed in a context of extreme urgency, within a time frame during which the entire healthcare team is fully mobilized in preparation for the caesarean section.

Although online randomization on a website is fast, the extreme urgency in which the study takes place prohibits its use. Therefore, we needed to set up early randomization. Three treatments, lidocaine alone or lidocaine-bicarbonate, will be prepared and labeled in a randomly defined order every 24 h. The use of a 24-h period is based on product stability. Eligibility criteria in the trial will be scrupulously checked before using the labeled products to limit exclusions after randomization as much as possible. To achieve this objective, the number of inclusion and exclusion criteria has been voluntarily limited.

Another element that will be studied in the analysis of baseline population characteristics will be to compare thermal sensory levels before injection in the two groups to overcome a significant confounding bias. Indeed, beyond the extension solution used, the pre-existing sensory level of epidural analgesia is a determining factor in the speed and extent of epidural extension and ultimately its success or failure. The randomization process is expected to offer a similar distribution of sensory levels before injection, but it will be necessary to ensure that there is no imbalance.

Alkalinization of local anesthetics could improve the success rate of epidural extension by reducing the onset time of surgical anesthesia and therefore the rate of recourse to general anesthesia.

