### Sample size {14}

No previous study has investigated the use of general anesthesia after epidural extension with an alkalinized local anesthetic solution in extremely emergency caesarean sections during labor. However, a preliminary retrospective clinical audit conducted in 2019 at the Bordeaux University Hospital maternity ward found that the rate of recourse to general anesthesia was 100% (4 out of 4) in the lidocaine alone group, versus 0% (0/7) in the lidocaine-bicarbonate group. Although the sample size was small, the difference was significant (*p*=0.003). Therefore, caution should be exercised when using this preliminary result to calculate the number of subjects required for the current trial. Conservatively, assuming a general anesthesia conversion rate of 80% in the control group and 40% in the experimental group, 44 patients will be required in the lidocaine-bicarbonate group and 22 patients in the lidocaine group, for a total of 66 patients in a 2:1 ratio. The number of subjects required was calculated for a two-sided comparison test of two proportions with a 90% power and a 5% risk alpha.

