## Statistical methods

### Statistical methods for primary and secondary outcomes {20a}

The primary statistical analysis will compare the proportion of general anesthesia use between groups LEB and LE. The two groups will be compared using a chi-squared test, a corrected chi-squared test, or a Fisher’s exact test depending on the distribution of the theoretical numbers under the assumption of independence. The two-sided 95% confidence interval will be estimated for each group according to the exact binomial distribution.

Secondary outcomes will be compared according to the following principles. Quantitative variables will be compared by Student’s *t* test, Student’s test for unequal variances, or a non-parametric Wilcoxon test depending on the conditions of application of these tests. Linear regression models will be used to adjust for the major confounders. The assumptions of the model (normality and homoscedasticity of the residuals, linearity of the association for the quantitative factors) will be systematically verified. A transformation of the criteria may be envisaged in the event of deviation from the models’ hypotheses.

Qualitative variables will be compared by a chi-squared test, a corrected chi-squared test, or a Fisher’s exact test according to the distribution of the theoretical numbers under the hypothesis of independence. Logistic regression models will be used to adjust for the major confounders. The hypothesis of the models (log-linearity of the association for the quantitative factors) will be systematically tested.

A graphical representation will be associated as much as possible with the analyses

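### A baseline comparison of pre-injection sensory level cannot overcome confounding; prespecify an adjusted supportive analysis of the primary outcome

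*Protocol article*

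**What the plan says.** The Discussion of the protocol article says that the block level already present before the study injection largely governs how fast and how far the extension spreads, and in the end whether it works. Its planned response is to "compare thermal sensory levels before injection in the two groups to overcome a significant confounding bias". It expects randomisation to balance this level but adds that "it will be necessary to ensure that there is no imbalance". It names no action if an imbalance appears.

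Under Statistical methods {20a}, "The primary statistical analysis will compare the proportion of general anesthesia use between groups LEB and LE", and "The two groups will be compared using a chi-squared test, a corrected chi-squared test, or a Fisher’s exact test", chosen by expected counts. Linear and logistic regression for confounders come only after the sentence "Secondary outcomes will be compared according to the following principles", and the confounders are not named. Sequence generation {16a} stratifies by centre alone. Sample size {14} is computed "assuming a general anesthesia conversion rate of 80% in the control group and 40% in the experimental group", for a "two-sided comparison test of two proportions with a 90% power and a 5% risk alpha", "for a total of 66 patients in a 2:1 ratio".

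**The concern.** The one baseline factor that the article singles out as decisive for the primary outcome is handled neither in the randomisation nor in the primary analysis. The only step described for it is a table or test of baseline balance, and the article credits that step with removing bias. It cannot do so. A non-significant comparison is weak evidence of balance in a trial of this size, and a significant one changes nothing in the estimate. Nor can anyone ensure balance once women have been randomised.

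Two things are at stake. The first is how the single realised estimate will be read if the arms happen to differ on this factor. The second is precision that a planned adjustment could supply.

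**Working it through.** **1. The plan's own figure.** Inputs from Sample size {14}: 80% versus 40%, two-sided alpha 5%, power 90%, allocation 2:1. With pooled variance and no continuity correction:

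- Pooled rate = (0.80 + 2 × 0.40)/3 = 0.533.
- Control n = [1.96 × √(1.5 × 0.533 × 0.467) + 1.282 × √(0.16 + 0.24/2)]² / 0.40² ≈ 22.0, so 22 + 44 = 66.
- Power at 22/44 by the same formula is 90.0%. Exact enumeration gives 89.1% for the uncorrected chi-squared test, 87.4% for Fisher and 84.8% with Yates' correction.
- The smallest expected count at the design rates is 22 × (1 − 35.2/66) ≈ 10.3, so the uncorrected test would normally apply.

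The stated 66 and 90% therefore reproduce, and they belong to the unadjusted test.

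**2. What the baseline comparison can detect.** For a covariate in SD units (normal approximation):

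- SD of the between-arm difference = √(1/44 + 1/22) = 0.261.
- P(|difference| > 0.25) = P(|Z| > 0.25/0.261) = 0.34.
- A 5% test flags only beyond 1.96 × 0.261 = 0.51.
- Chance of an imbalance above 0.25 SD that is not flagged: 0.34 − 0.05 = 0.29.

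**3. What an imbalance does, and what adjustment gives.** The article does not say how strongly sensory level predicts general anaesthesia. The assumption is a standard normal covariate with log-odds per SD of 0, 0.7 or 1.5 (odds ratio 1, about 2 or about 4.5), with marginal rates held fixed. For each scenario 4,000 trials of 22 versus 44 were simulated. The crude chi-squared test was compared with a likelihood-ratio test from a logistic model containing arm and covariate.

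| Rates | OR per SD | Crude power | Adjusted power | Shift at +0.26 SD imbalance |
|---|---|---|---|---|
| 80% v 40% | 1 | 88.4% | 89.6% | 0.1 points |
| 80% v 40% | 2 | 88.9% | 92.1% | 2.3 points |
| 80% v 40% | 4.5 | 87.4% | 96.6% | 5.1 points |
| 80% v 50% | 1 | 67.7% | 70.9% | 0.1 points |
| 80% v 50% | 2 | 67.1% | 74.4% | 2.8 points |
| 80% v 50% | 4.5 | 67.5% | 82.4% | 5.0 points |

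With equal rates in both arms (80% or 50%) and odds ratios of 2 to 4.5, the shift was 2.7 to 5.8 points.

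- **Validity of the crude test:** its type I error was 4.4% to 5.3%. The mean crude risk difference was 0.396 to 0.400 against a true 0.40.
- **Inflation in the adjusted test:** its type I error was 5.0% to 6.3%. A covariate with no effect still appeared to add 89.6 − 88.4 = 1.2 points at 80% v 40% and 70.9 − 67.7 = 3.2 points at 80% v 50%.
- **Precision, which does not depend on the test's type I error:** at 80% v 40% the SD of the risk difference fell from 0.113 to 0.110 (odds ratio 2) and from 0.115 to 0.101 (odds ratio 4.5). The variance reductions are 1 − (0.110/0.113)² ≈ 5% and 1 − (0.101/0.115)² ≈ 23%.

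**The case against.** A reader might infer that bias persists in the primary result, since the article itself speaks of confounding. The documents do not support that. Allocation is randomised, and a chance difference in a baseline variable is not confounding bias. The crude test keeps its size and the estimate is right on average. Only a shift conditional on the realised imbalance remains. It sits inside a crude standard error of √(0.16/22 + 0.24/44) ≈ 11 points and is small beside a 40-point target.

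A reader might also infer that power is lost. It is not: the 90% was planned for the unadjusted test. Nor does the article say that the analysis will change once imbalance has been seen, so no data-driven rule can be attributed to it.

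Other objections carry weight:

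- An unadjusted primary test is a conventional choice. An analysis plan that is not shown may already name covariates.
- The prognostic strength is assumed. Excluding non-functional epidurals may narrow the range of sensory levels and weaken the association.
- The audit gave 4/4 versus 0/7. Results near that pattern would make ordinary logistic regression unstable, whereas Fisher's test would still work.
- Recruitment began in July 2022, so replacing the primary test is harder to defend than adding an analysis.

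These points limit the claim and shape the remedy. They do not rescue the statement that a comparison overcomes confounding, which is wrong as written and has no counterpart in the primary analysis under {20a}.

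**Conclusion.** The point holds in a limited form. The Discussion assigns to a baseline comparison a task that it cannot perform, and the primary analysis makes no use of a factor that the article regards as decisive. The planned test remains valid and its stated power reproduces.

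The exposure is a shift of about 2 to 6 points at an imbalance of about 0.25 SD. The forgone gain is about 3 to 9 points of power at 80% versus 40%, part of which is small-sample inflation. Both ranges rest on assumed odds ratios of 2 to 4.5 per SD; with no association the shift vanishes and there is no real gain. They also assume sound randomisation. The simulation adjusted for the covariate alone, without centre, and did not evaluate the confidence interval or the small-sample remedies proposed below. This is a minor to moderate point about precision and interpretation.

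**What to change.** 1. Delete the statement that comparing sensory levels overcomes confounding, and the demand to ensure no imbalance. Present the levels descriptively by arm.
2. Keep the planned test as primary. Prespecify, whatever balance is observed, a key supportive analysis of the primary outcome: logistic regression on arm, centre and pre-injection thermal sensory level (dermatome as a numeric score). Report it as a standardised risk difference with 95% CI, that is, predicted risks averaged over all women under each arm.
3. Use a permutation p-value or penalised likelihood, named in advance, to deal with small-sample error and possible separation.
4. State a rule for a missing sensory level. Section {20c} imputes only the primary endpoint (apart from partial dates), so women without a recorded level would otherwise drop out of the model.
5. Date the change before outcome data by arm are examined, because {17a} leaves the biostatisticians unblinded.

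The cost is a slightly more complex analysis and some text. The article already plans to analyse the variable at baseline, so no new measurement is needed. The sponsor would have to judge whether the addition counts as a substantial modification under {25}. If an analysis plan not shown already contains this analysis, only the Discussion wording needs correcting.

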## Trial status

Protocol version number and date: version 1.2 (March 15, 2022)

Date recruitment began: July 7, 2022

When recruitment will be completed: Q3 2023 or Q4 2023

## Data Availability

Only the database managers, the team in charge of clinical research at the Bordeaux University Hospital and the auditors will have direct access to the database.

## Abbreviations

PACU: Post-Anesthesia Care Unit
SFAR: Société Française d’Anesthésie-Réanimation – French Society of Anaesthesia and Critical Care
CNGOF: Collège National des Gynécologues et Obstétriciens Français - French national college of obstetricians and gynecologists
USMR: Unité de Soutien Méthodologique à la Recherche - Research Methodology Support Unit
ANSM: Agence nationale de sécurité du médicament - French Agency for the Safety of Health Products
